### Baseline assessments

We will first explain the study to each subject and obtain oral and written consent. The study design, experiments, and consent forms were approved by the institutional review board of the University of Hawaii at Manoa (CHS#20523). A detailed medical and drug use history and physical and neuropsychiatric evaluations will be performed, along with screening blood tests to assess general health, including complete blood cell count, chemistry panel, thyroid function tests, hepatitis C and HIV serology. An electrocardiogram will be obtained to screen for significant cardiac abnormalities; subjects will be referred for further cardiac evaluations should significant abnormalities be found. Psychiatric and quality-of-life evaluations will be additionally performed through a battery of questionnaires and self-reported assessments; some will be repeated after training (Table 1).

**Table 1 Tab1:** Questionnaires and interviews

	Outcome measures	Baseline	1 month after training	6 months after training
Hollingshead Four Factor Index [90]	Socioeconomic status; combination of race, ethnicity, occupational status and education level	✓		
Psychiatric assessments				
Symptom Checklist–90–revised	Psychological and emotional distress	✓	✓	✓
Center for Epidemiological Studies–Depression Scale [91]	Depressive symptoms and to rule out possible major depression	✓	✓	✓
Substance use assessments				
Substance Abuse Subtle Screening Inventory-3 [92]	Identification of individuals with a high probability of having a substance use disorder	✓	✓	✓
Urine toxicology	Substance usage	✓	✓	✓
Quality-of-life assessments				
Independent Activity of Daily Living [93]	Ability to carry out daily functions	✓	✓	✓
Behavior Rating Inventory of Executive Function–Adult Version	Executive function	✓	✓	✓
Pittsburgh Sleep Quality Index [94], Epworth Sleepiness Scale [95]	General level of daytime sleepiness	✓	✓	✓
PROMIS®	Global health status and pain intensity, interference and behavior	✓	✓	✓
Medical Outcomes Study HIV Health Survey [96]	Health status for HIV-positive patients	✓	✓	✓
World Health Organization Quality of Life [97]	Well-being and quality of life	✓	✓	✓
Biospecimens				
Blood	DNA and genotyping	✓		
Blood and serum	Cytokines and monoamines and neurometabolite measurements	✓	✓	✓
Cerebrospinal fluid	Cytokines monoamines and neurometabolite measurements	✓	✓	

Subjects with significant psychiatric symptoms will be further assessed by a qualified physician, to determine whether psychiatric referral is necessary. Those with suicidal thoughts or acute intoxication will be sent to the psychiatric emergency department. Subjects with significant medical problems, screening blood test abnormalities, or electrocardiographic abnormalities will be referred to their primary care physicians, other clinics or the emergency department as needed.

### Neuropsychological evaluation

The 2 hour long neuropsychological test battery is designed to detect deficits in (1) working memory and attention, which implicate networks in frontal and parietal regions; (2) decision making and inhibition, which involve primarily the anterior cingulate and orbitofrontal cortices; and (3) motor and psychomotor speed, which are associated with alterations in the basal ganglia and cerebellum.Diagnosis of HAND or HAND-equivalent at baseline will be determined using z-scores from seven cognitive domains, adjusted for age and education, and derived from our existing normative database (including ≈ 450 healthy seronegative controls tested with the same protocol). HAND classification will be made according to the Updated Research Nosology for HAND [63] by physicians for all subjects. The HIV-positive and seronegative control groups will be matched by their cognitive status (i.e., global z-score) (Table 2).

**Table 2 Tab2:** Neuropsychological assessments (non-trained working memory tests)

	Baseline	1 month after training	6 months after training
Attention, working memory			
Paced Auditory Serial Addition Test	✓		
Wechsler Adult Intelligence Scale IV (Digit Span, Letter Number Sequencing, Arithmetic, and Digit-Symbol Coding)	✓	✓	✓
California Computerized Assessment Package	✓	✓	✓
Delis–Kaplan Executive Function System	✓	✓	✓
Abstraction, executive functions			
Stroop Color Interference Test	✓		
Trail Making Test Part B	✓		
Fluency			
Controlled Oral Word Association Test (FAS)	✓		
Design Fluency Tests (Ruff Figural Fluency)	✓		
Memory			
Rey Auditory Verbal Learning Test Delayed Recall	✓	✓	✓
Rey Osterrieth Complex Figure Test	✓	✓	✓
Speed of information processing, psychomotor speed			
Symbol Digit Modalities Test	✓		
Trail Making Test Part A	✓		
Motor skills			
Grooved pegboard test (dominant and non-dominant hand)	✓		
Verbal, language			
Wechsler Adult Intelligence Scale, fourth edition, verbal comprehension index	✓		
Wechsler Test of Adult Reading	✓		
Wechsler Adult Intelligence Scale	✓		
Wechsler Memory Scale IV			
Spatial span	✓	✓	✓
Visual, verbal immediate and long-term memory	✓	✓	✓
Mental control	✓	✓	✓General intelligence: the Wechsler Test of Adult Reading will provide an estimate of premorbid intellectual functioning during our screening procedure to ensure that the subjects have a verbal intelligence quotient > 80 and can provide consent. The Wechsler Adult Intelligence Scale IV will be used to evaluate general cognitive ability (intelligence quotient) for all subjects at baseline.Assessments of changes in working memory, other cognition and function (primary outcomes) will be administered repeatedly at baseline, 1 month after training (either adaptive working memory or ‘active control’ training condition), and 6 months after the adaptive working memory training. Alternative word lists or stories will be used for repeated testing. Table 2 shows the tests involved in the trained working memory tests, which will include the ‘start index, maximum index, and improvement index’, the non-trained working memory tests and the transfer of working memory capacity gain to other cognitive functions.

For the non-trained working memory tasks, no practice effects are expected [64]. However, for the other neuropsychological tests, variable degrees of practice effects will occur with test–retest [65]; we will control for such practice effects by performing the same tests before and after CWMT in both HIV-positive and seronegative control subjects.

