## Methods/design

The proposed study uses a 2 × 2 repeated-measures analysis of covariance (ANCOVA) design to evaluate the effects of 5 weeks of CWMT, adaptive versus ‘active control (fixed low level)’ training, as assessed by the improvement index (generated from task performances within the CWMT), neurocognitive testing, BOLD-fMRI measurements, cerebrospinal fluid neuroinflammatory proteins, monoamine, and metabolite levels. We propose to enroll 60 HIV-infected individuals and 60 seronegative healthy participants, with 30 adaptive and 30 active-control-training subjects randomized in each group (Fig. 1). HIV-positive and seronegative subject groups will be matched by age, sex, education, socioeconomic status, and cognitive status (matched by global cognitive score from the seven cognitive domains tested), as well as other co-variates (e.g., nicotine smoking and other substances abused). Based on the initial screening evaluations, subjects who fulfill all study criteria will be scheduled for a baseline neuropsychological evaluation, MRI-fMRI scans, and a lumbar puncture.

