## Dissemination plan

At the completion of this trial, we plan to submit several manuscripts to peer-reviewed journals including;‘Neural correlates of adaptive working memory training in HIV patients’: this paper will report on the interim findings from the primary outcome measures, including improvements on working memory performance and neural efficiencies, 1 month and 6 months after the adaptive version of CWMT, to assess the gain and maintenance of working memory improvements after training. Some of the secondary contrast results, including scoring on the Behavior Rating Inventory of Executive Function–Adult Version and *LMX1A* genotype effects, will also be reported. These findings may lead to a larger study to validate whether CWMT can be used as an adjunctive therapy for HAND.‘Computerized working memory training in HIV patients: a double-blind active control study’: this paper will be written at the completion of subject enrollments. We will compare the effects of adaptive versus fixed low level of CWMT on the primary outcome measures, at 1 month and 6 months after training compared with baseline assessments. This will provide further evidence of whether CWMT is effective for working memory and attention deficits in HIV patients.This paper will also report on the findings after the double-blind active control study to evaluate the efficacy of CWMT on the secondary outcome measures, including scores on the the Center for Epidemiological Studies–Depression Scale, Revised, and the Symptom Checklist–90–revised, and ability to conduct activities of daily living (Independent Activity of Daily Living assessment and the Behavior Rating Inventory of Executive Function–Adult Version) before and after CWMT.This paper will report on possible improvements in cerebrospinal fluid neuroinflammatory proteins (chemokines and cytokines) and neurochemicals (dopamine and serotonergic levels and their metabolites) after CWMT. Since only half of the participants might consent to the lumbar punctures, we may need to combine results from the adaptive training group and the fix-low-level training group to evaluate the training effects on these cerebrospinal fluid measurements.

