#### BOLD-fMRI studies (Aim 2)

BOLD-fMRI has been used to evaluate brain changes in HIV-positive patients for more than a decade. BOLD-fMRI signals in these individuals are altered during tasks that require working memory [74, 75] and visual attention [74, 76]. A prior study showed that HIV patients had a lower working memory network capacity, which was further affected by other concurrent brain activities (e.g., louder acoustic noise proportionally decreased working memory activation); hence, they would be distracted more easily by other activities in their daily life [75]. Hence, we expect that subjects with normal cognition (higher working memory capacity) will show greater improvement than those with cognitive deficits.

BOLD-fMRI signals during working memory tasks were also greater in cognitively normal HIV-positive subjects compared with seronegative controls [77], as well as in HIV-positive subjects receiving antiretroviral medications compared with both HIV-negative and antiretroviral medication-naïve subjects and seronegative controls [6]. Greater BOLD-fMRI signals in HIV patients were predicted by higher levels of glial metabolites (myoinositol, total creatine, and choline) [78]. These findings suggest that ongoing increased neuroinflammation in HIV patients necessitates greater usage of the working memory network. Such neuroinflammation appeared to be ongoing despite stable antiretroviral treatments, since HIV-positive subjects showed increased BOLD-fMRI signals within the visual attention network in a one-year longitudinal follow-up study (suggesting decline efficiency), while matched seronegative controls showed decreased BOLD-fMRI signals (consistent with a test–retest practice effect) [79]. Therefore, this study will also explore how neuroinflammation as assessed by cerebrospinal fluid inflammatory markers is related to BOLD-fMRI signals before and after working memory training.

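### The HIV versus seronegative comparison named as the control for practice effects cannot separate practice from training gain; the randomised active-control arm can, and the first planned paper should use it.

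*Protocol article*

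**What the plan says.** All places are in the protocol article.

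- **Neuropsychological evaluation.** On the non-trained tasks: "For the non-trained working memory tasks, no practice effects are expected". By contrast, "for the other neuropsychological tests, variable degrees of practice effects will occur with test–retest", and the stated remedy is that "we will control for such practice effects by performing the same tests before and after CWMT in both HIV-positive and seronegative control subjects". A further mitigation is given: "Alternative word lists or stories will be used for repeated testing". The repeated tests fall at baseline, "1 month after training (either adaptive working memory or ‘active control’ training condition), and 6 months after the adaptive working memory training".
- **Methods/design.** Both serostatus groups are trained, "with 30 adaptive and 30 active-control-training subjects randomized in each group".
- **Statistical analysis.** The repeated-measures model has HIV status and training condition between subjects and time within subject.
- **Expected findings.** The Aim 1 hypothesis is that adaptive training gives more gain than active control. The Aim 2 prediction of lower activation is made against baseline and also against active control.
- **Dissemination plan.** The first manuscript presents interim results at 1 and 6 months after the adaptive version, "to assess the gain and maintenance of working memory improvements after training". The comparison of adaptive with fixed training on the primary outcomes belongs to a later paper.

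**The concern.** A control for practice must be a group that takes the same tests on the same schedule without the treatment under study. The seronegative group is not such a group, because it is randomised to the same two training conditions as the HIV-positive group. Its change in the adaptive arm is practice plus training, exactly as in HIV-positive subjects. The group that does isolate practice is the fixed low-level arm, and the sentence on practice effects does not mention it.

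At stake is the meaning of the word gain. Where change from baseline within the adaptive arm is reported as training gain, ordinary improvement on retest is counted as a benefit of the intervention. The first manuscript, as described, invites that reading for both cognitive scores and brain activation.

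**Working it through.** **1. What each comparison estimates.** Let P be the practice shift and T the effect of adaptive over fixed training, both in SDs of change and equal across serostatus. Neither value is in the article; P = 0.3 and T = 0.4 are assumed for illustration.

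| Comparison | Expected value | P = 0.3, T = 0.4 | P = 0.3, T = 0 |
|---|---|---|---|
| HIV minus seronegative, adaptive arm | (P + T) − (P + T) | 0 | 0 |
| Before-after, adaptive arm | P + T | 0.7 | 0.3 |
| Adaptive minus fixed | (P + T) − P | 0.4 | 0 |

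The serostatus comparison returns 0 whether or not training works. If P or T differs by serostatus, it returns a mixture of the two differences. Only the last row returns T.

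**2. The article's own sample sizes are before-after sizes.** The Participants section gives about 17 HIV-positive subjects for an effect size of 0.7, and 26 for 0.58, at 80 % power, two-sided (alpha 0.05 assumed, as in the Statistical analysis section).
- Paired, normal formula n = ((1.960 + 0.842)/d)²: 16.02, so 17, for 0.7; 23.3, so 24, for 0.58.
- Paired t-test: 19 and 26.
- Two-arm comparison, normal formula: 33 and 47 per arm.

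The stated figures match the paired calculations within 2 subjects and do not match the two-arm one. The pilot effects are therefore within-person changes and carry any practice present. They concern working memory tests, where the article assumes no practice, and BOLD signal.

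**3. Size of the exposure in an uncontrolled reading.** The article expects 50 HIV-positive subjects at 1 month, so 50/2 = 25 in the adaptive arm. Take T = 0 and a paired t-test at two-sided 0.05. The noncentrality is P√n = 5P, with 24 degrees of freedom and critical value 2.064.

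| Assumed P | Noncentrality | Probability of a significant change |
|---|---|---|
| 0.2 | 1.0 | 16 % |
| 0.3 | 1.5 | 30 % |
| 0.4 | 2.0 | 48 % |

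With 50 adaptive subjects pooled over serostatus, the same calculation gives 28 %, 55 % and 79 %. With no practice it would be 5 %.

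**4. Power of the contrast that removes practice** (normal approximation, two-sided 0.05, effect in SDs of change):

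| Subjects per arm at 1 month | d = 0.7 | d = 0.58 |
|---|---|---|
| 25 (HIV-positive only, 50/2) | 0.70 | 0.54 |
| 51 (pooled over serostatus, 102/2) | 0.94 | 0.83 |

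These are upper values, because a before-after effect that includes practice overstates the between-arm effect. At an assumed between-arm d of 0.4, power is 0.29 with 25 per arm and 0.52 with 51 per arm.

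**The case against.** The strongest reply is that the trial already controls practice. Subjects are randomised to adaptive or fixed training within each serostatus group, both arms are tested at baseline and 1 month, and training condition and time are both in the model. The criticised sentence specifies no contrast, and alternate word lists and stories reduce practice on some tests. This stands for the main comparison at 1 month. A reader might infer that the trial's efficacy result is mixed with practice; the documents do not support that.

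Three further readings also go too far.

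- *The article contradicts itself on practice.* The BOLD section says that in an earlier one-year study "matched seronegative controls showed decreased BOLD-fMRI signals (consistent with a test–retest practice effect". That concerns brain activation in the visual attention network, whereas the no-practice statement concerns behavioural working memory scores. The two can both be true. Nor does the article plan to read every BOLD decrease as efficiency, since its prediction is also relative to active control.
- *The 16 % to 48 % are the trial's false-positive rates.* They apply only to an unadjusted paired test in one arm under assumed practice. The planned factorial model has an expected contrast of 0 when training does nothing, and the article also specifies a modified Bonferroni procedure.
- *The first manuscript excludes the control arm.* The description is short, concerns interim findings and does not say so. It mentions no control comparison and assigns that comparison to another paper, so the ambiguity is real but confined to the interim report.

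**Conclusion.** The point holds in limited form. The sentence on practice effects names a comparison that cannot do what is claimed for it, because both serostatus groups are trained. The design contains the right control and the main analysis uses it, so the efficacy comparison at 1 month is not compromised, provided practice is similar in the two training arms.

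The practical risk is in before-after results from the adaptive arm, notably the first manuscript. There, an uncontrolled test in 25 subjects with no training effect would be significant in about 16 % to 48 % of trials for practice shifts of 0.2 to 0.4 SD. Those shifts are assumptions, and alternate test forms may make the true ones smaller.

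At 6 months the protection is weaker. Active controls may move to open-label adaptive training after the 1-month visit, and the test schedule ties the 6-month visit to adaptive training, although the Participant randomization section also mentions a 6-month follow-up for active control.

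**What to change.** 1. In Neuropsychological evaluation, replace the sentence on controlling practice with: *Practice effects are removed by comparing change in the adaptive arm with change in the randomised active-control arm (training-by-time contrast, pooled over serostatus with serostatus in the model).*
2. Report the active-control arm's change on every repeated test, including the non-trained working memory tasks. This checks the no-practice assumption with the trial's own data; the assumption need not be withdrawn beforehand.
3. In the Dissemination plan, have the interim paper either give the adaptive-versus-active-control contrast for cognitive and BOLD outcomes, or describe change from baseline without calling it training gain.

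The contrast need not be made separately within each serostatus group. That is not required to remove practice and would lower power, from 0.94 to 0.70 at d = 0.7 and from 0.83 to 0.54 at d = 0.58.

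The cost is small: a change of wording and no new data. The interim paper must include the active-control results or make a weaker claim.

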### Cognitive intervention using Cogmed® RM

The Cogmed® RM (Table 3) was developed for school-aged children; however, we chose this version for our adult participants since it is more colorful and appealing to the participants than the adult version (Cogmed® QM). The training program consists of 25 training sessions (minimum of 20 required), 30–40 minutes per day, 4–5 days per week over a 5–8 week period [35]. Subjects will perform either the ‘active control’, with a fixed low level across each task, or an ‘adaptive’ version, with increasing difficulty for the working memory tasks. The training will be performed either in the participants’ homes, or at the research laboratory. We will ensure that participants have high-speed internet access. Subjects will be trained using verbal and non-verbal working memory tasks that involve: (1) maintenance of several stimuli at the same time; (2) short delays during which the representation of stimuli should be held in the working memory; (3) unique sequencing of stimulus order in each trial. Training will be supplemented with weekly guidance by trained ‘coaches’, who can review subjects’ progress online and will telephone them to give feedback, motivation, and advice to optimize their training experience.

**Table 3 Tab3:** Description of the 12 modules in Cogmed® Working Memory Training

Task	Description
Verbal working memory (with visuospatial components)	
Input module (numbers)	A panel with 1 to 9 is shown. Numbers are presented aurally and light up on the panel sequentially. Participants then have to click on the numbers in the reversed sequence.
Input module with lid (hidden numbers)	Same as previous task, except numbers are presented aurally only, since they are covered by a lid, which opens when all the numbers are read.
Stabilizer (letters)	A circle of lamps is shown. A sequence of letters is presented aurally along with specific lamps that light up. Participants are then presented with a letter in the middle of the circle, and have to click on the lamp that lit up.
Decoder	Letters are read sequentially along with a lamp that lights up. The participant then has to reproduce the sequence by selecting one letter from three possible letters below each lamp.
Visuospatial working memory	
Visual data link (grid)	Lamps light up sequentially in a 4 × 4 grid, and the participant must reproduce the sequence by clicking on the lamps in the same order afterwards.
Rotating data link (rotating grid)	Same as the grid task above, except that after the lamps light up, the entire board rotates 90° and the participant has to click on the sequence of lamps in the rotated grid.
Data room (three-dimensional grid)	Lamps will light up sequentially in a three-dimensional box (view from the front), with four lamps per plane, and the participant must reproduce the sequence by clicking on the lamps.
Three-dimensional cube	The program zooms in on different planes of a cube (four squares on the back and two squares on the other planes) as they light up sequentially. The participant must click the squares in the correct order.
Rotating (rotating dot)	Lamps light up sequentially on a circle, which rotates slowly clockwise, and the participant has to reproduce the sequence by clicking on the lamps on the moving circle.
Sorter	Boxes open to reveal numbers out of order and the participant must click on the boxes in the correct numerical order.
Asteroids	Asteroids light up sequentially while moving around the screen and the participant must reproduce the sequence by clicking on the moving asteroids.
Space whack	Craters emit puffs of smoke sequentially. The participant must remember the order that the puffs appeared, in order to click on the alien that will pop out of the crater in the same sequence.

